## Abstract

**Background:**

Nationally, symptomatic heart failure affects 1.5-2% of Canadians, incurs $3 billion in hospital costs annually and the global burden is expected to double in the next 1–2 decades. The current one-year mortality rate after diagnosis of heart failure remains high at >25%. Consequently, new therapeutic strategies need to be developed for this debilitating condition.

**Methods/Design:**

The objective of the Alberta HEART program (http://albertaheartresearch.ca) is to develop novel diagnostic, therapeutic and prognostic approaches to patients with heart failure with preserved ejection fraction. We hypothesize that novel imaging techniques and biomarkers will aid in describing heart failure with preserved ejection fraction. Furthermore, the development of new diagnostic criteria will allow us to: 1) better define risk factors associated with heart failure with preserved ejection fraction; 2) elucidate clinical, cellular and molecular mechanisms involved with the development and progression of heart failure with preserved ejection fraction; 3) design and test new therapeutic strategies for patients with heart failure with preserved ejection fraction. Additionally, Alberta HEART provides training and education for enhancing translational medicine, knowledge translation and clinical practice in heart failure. This is a prospective observational cohort study of patients with, or at risk for, heart failure. Patients will have sequential testing including quality of life and clinical outcomes over 12 months. After that time, study participants will be passively followed via linkage to external administrative databases. Clinical outcomes of interest include death, hospitalization, emergency department visits, physician resource use and/or heart transplant. Patients will be followed for a total of 5 years.

**Discussion:**

Alberta HEART has the primary objective to define new diagnostic criteria for patients with heart failure with preserved ejection fraction. New criteria will allow for targeted therapies, diagnostic tests and further understanding of the patients, both at-risk for and with heart failure.

**Trial registration:**

ClinicalTrials.gov NCT02052804.

## Background

Cardiovascular disease is one of the primary causes of death and disability in Canada and is a leading cause of death worldwide (http://www.who.int/chp/chronic_disease_report/en/). While advancements in medical and surgical therapies have improved cardiac mortality, these advances have led to an increase in the incidence and prevalence of heart failure (HF)
[1]. At the national level, symptomatic HF affects 1.5-2% of Canadians, incurs $3 billion in hospital costs annually, and the global burden is expected to double in the next 1–2 decades
[2,3]. In addition, the current one-year mortality rate after diagnosis of HF remains disturbingly high at >25%
[4,5], and the condition has the worst effect on quality of life of any chronic medical condition
[6]. Consequently, new therapeutic strategies need to be developed for this debilitating condition.

HF is a clinical syndrome characterized by specific symptoms (e.g. shortness of breath and reduced exercise capacity) as well as physical examination findings. HF has traditionally been described by a depressed ejection fractions ranging from <30-45% with <40% used as a criteria that is generally used in clinical trials and guidelines
[7-9]. However, up to 50% of patients presenting with HF have preserved systolic function and are thus diagnosed with “diastolic HF”
[3,10,11]. It is now recognized that a diverse group of cardiac diseases give rise to this condition and thus the clinical and research community has more appropriately renamed “diastolic HF” as HF with a preserved ejection fraction (HF-PEF) or HF-preserved systolic function (HF-PSF). Regardless of the nomenclature, no therapy has been proven in randomized clinical trials to reduce the morbidity or mortality of HF-PEF and, as such, no guideline endorses a specific therapy targeted at HF-PEF
[8,9,12,13]. While the lack of an available agent is multi-factorial, we believe that the current criteria used for defining HF-PEF are inadequate. This may skew patient stratification in HF trials and prevent the identification of therapies that may actually have benefit in HF-PEF.

The objective of the Alberta HEART program (http://albertaheartresearch.ca) is to develop novel diagnostic, therapeutic and prognostic approaches to patients with HF-PEF. We hypothesize that novel imaging techniques and biomarkers will aid in describing HF-PEF. Furthermore, the development of new diagnostic criteria will allow us to: 1) better define the risk factors associated with the HF-PEF; 2) elucidate the clinical, cellular and molecular mechanisms involved with the development and progression of HF-PEF; 3) design and test new therapeutic strategies for patients with HF-PEF. Alberta HEART additionally provides training and education program for enhancing translational medicine, knowledge translation and clinical practice in heart failure.

## Methods/design

### Trial status

The study is approved by the Health Research Ethics Boards at the University of Alberta, Covenant Health and the University of Calgary. Recruitment began in January 2010 and as of March 31, 2014, 649 patients have been enrolled. ClinicalTrials.gov NCT02052804.

### Study design

This is a prospective observational cohort study of patients with, or at risk for, HF.

### Study population

Patients are adults (i.e. aged over 18 years of age) recruited from Alberta (population 4.0 million), principally in Edmonton and Calgary but also from rural regions. In order to enroll and study patients across the spectrum of risk of developing HF, with signs or symptoms mimicking HF, or with a diagnosis of HF, a broad recruitment strategy that categorizes patients into 5 distinct groups is underway. The 5 distinct groups are:

1. High-risk of developing HF-PEF but no clinically overt HF: Patients will have one or more of the following: hypertension (≥3 medications or LVH on ECG or left ventricular mass index > gender-matched upper limit normal on an imaging test); diabetes (>45 years of age); atrial fibrillation; or obesity (body mass index >30). Patients will be generally asymptomatic (no dyspnea or fatigue) and have no known prior HF or other cardiovascular disease.

2. High-risk of developing HF-PEF with other clinically overt disease: Patients with other cardiovascular diseases will be recruited including atrial fibrillation, chronic coronary artery disease (including those with a recent acute coronary syndrome > 2 weeks prior), and COPD.

3. Patients with known HF-PEF: These are patients who have been diagnosed with HF-PEF based on the clinical phenotype of symptoms consistent with HF, and a preserved ejection fraction. Patients with the clinical diagnosis of HF-PEF and an ejection fraction >45% will be enrolled in this study from the heart failure clinics in Alberta. For further definition, the group will be divided into 3a (LVEF always ≥ 45%; no right ventricle involvement), 3b (LVEF previously <45%, now ≥ 45%; with or without right ventricle involvement), and 3c (LVEF always ≥ 45%; right ventricle involvement or pulmonary hypertension (TAPSE <16 mm, PASP > 35 mmHg, or clinical judgment)).

4. Patients with known systolic HF: Patients with systolic HF often have abnormalities in the mechanical diastolic function and are necessary to complete the spectrum to act as a comparator for group 3. An ejection fraction <45% and a diagnosis of HF will be included.

5. Healthy age- and gender-matched controls: Patients with no evidence of coronary artery disease, hypertension, diabetes mellitus, organ disease or replacement therapies; no evidence of inflammatory or autoimmune conditions and not on cardiac medications.

Patients will be recruited from HF and other clinics across Alberta. Control patients are recruited through referrals from patients, clinicians and the broader community across Alberta via public advertising, media events and other public engagement. All patients signed informed consent and the study is approved by the Health Research Ethics Boards at the University of Alberta, Covenant Health and the University of Calgary. After consent, patients are enrolled and undergo comprehensive clinical, quality of life, biomarker, electrophysiologic and imaging assessments (Figure 
1). Patients are also eligible for substudy enrollment (see below). Patients are re-assessed at 6 and 12 months and longer-term clinical and outcome surveillance is planned. Data is managed on the Alberta Provincial Project for Outcome Assessment in Coronary Heart Disease platform (http://www.approach.org/).

**Figure 1 F1:**
[figure not shown]
Alberta HEART study design.

### Adjudication

Given the lack of a single accepted and validated definition for HF-PEF, the 3 most commonly used clinical criteria from landmark papers
[14-16] ongoing or completed trials
[17,18] or population studies
[3,10,11] will be evaluated for applicability to the development of new criteria (Table 
1). These criteria highlight two important points: (1) diagnostic uncertainty may exist and should be captured by any criteria proposed using a hierarchical methodology; and (2) time of evaluation may alter the certainty of the diagnosis as clinical findings (and non-invasive or invasive markers) may change with therapy or time. In addition, none of these 3 sets of criteria have been compared, or evaluated in the setting of other conditions, which may mimic symptoms of HF (e.g. lung disease, hypertension, diabetes, obesity, deconditioning).

**Table 1 T1:** Current diagnostic criteria for HF-PEF

**Definition**	**ESC **[12,14]	**Vasan et al. **[15]	**Zile et al.**[16,19]
**Signs or symptoms?**	Symptoms and signs of HF	Symptoms and signs, supporting laboratory tests and a typical clinical response to treatment^#^	Symptoms and signs of HF (by Framingham criteria)
**Ejection fraction**	LVEF > 50% and LVEDVI < 97 mls/m^2^	LVEF ≥ 50% within 72 hours of HF event**	LVEF > 50%
**Echo/Cath/Biomarker evidence of diastolic dysfunction?**	Yes	Yes***	Not required
		Abnormal LV relaxation, filling, distensibility indices on cardiac catheterization	

^#^with diuretics, with or without documentation of elevated LV filling pressure (at rest, on exercise, or in response to a volume load) or a low cardiac index; **downgraded to “Probable” if EF not defined in first 72 hours; ***downgraded to “Possible” if no Echo or Cath evidence; ESC, European Society of Cardiology.

Each of the three definitions will be applied to the cohort in order to evaluate the sensitivity, specificity, diagnostic accuracy, positive predictive value and negative predictive value using the diagnostic testing model based on Bossuyt *et al.*[20] and Sackett and Haynes
[21] and the reporting methods endorsed by STARD
[22] and QUADAS-2
[23]. A reference standard for HF-PEF is currently absent. Therefore, we have chosen to use a consensus panel approach using a panel of adjudicators blinded to the group of original recruitment (Figure 
2).

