### Sample size

Alberta HEART plans to recruit 700 patients with up to 100 patients in each of Groups 1, 2 and 5 and 200 patients in each of Groups 3 (HF-PEF) and 4 (known systolic HF). Given the lack of validated data from which to calculate a sample size, a convenience sampling technique has been used, recognizing that for some markers (e.g. imaging, exercise, biomarkers) the HEART study will be significantly powered, but for other outcomes (e.g. clinical outcomes) HEART will be underpowered. Nevertheless, the sample size will be increased as appropriate to meet the primary objectives of the study. An additional 100 age- and gender-matched controls (matched to group 3) will be been recruited and tested. Recruitment began in January 2010 and as of March 31st, 2014, 649 participants have been enrolled.

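### Raw PPV, NPV and overall accuracy of the three HF-PEF definitions would reflect recruitment targets and case mix, not a clinical population

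*Protocol article*

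**What the plan says.** The Adjudication section of the protocol article fixes both the measures and the population. "Each of the three definitions will be applied to the cohort", and the measures include "diagnostic accuracy, positive predictive value and negative predictive value using the diagnostic testing model", alongside sensitivity and specificity. The reference standard is a consensus panel blinded to the recruitment group.

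The cohort is assembled by disease group. Under Study population, "a broad recruitment strategy that categorizes patients into 5 distinct groups is underway": two at-risk groups (1 and 2), known HF-PEF (3), known systolic HF (4) and healthy controls (5). HF-PEF patients "will be enrolled in this study from the heart failure clinics in Alberta", while controls come through referral and public advertising. Under Sample size, "Alberta HEART plans to recruit 700 patients", made up of "up to 100 patients in each of Groups 1, 2 and 5 and 200 patients in each of Groups 3 (HF-PEF) and 4", and "a convenience sampling technique has been used". The same section adds: "An additional 100 age- and gender-matched controls (matched to group 3"). It is unclear whether these are Group 5 or come on top of the 700.

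The article does not restrict the predictive values to a clinically defined subset, re-weight them to an outside prevalence or caution about their interpretation.

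**The concern.** PPV and NPV depend on the share of diseased people among those tested. In a consecutive series of patients under suspicion, that share carries information about practice. Here it follows mainly from how many people the investigators chose to recruit per group. Changing the targets would change PPV and NPV even if the definitions performed identically.

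A second effect runs through specificity. Several groups contribute non-HF-PEF participants who can hardly meet the definitions, so pooled specificity, and every measure built on it, depends on how many of them were recruited.

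The stated primary objective is new diagnostic criteria, with a simple clinical tool if it proves valid. The three definitions are evaluated to inform those criteria. A PPV or NPV published without qualification is easily read as the probability of disease in the next patient with suspected HF-PEF, and these figures would not support that reading.

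**Working it through.** **Planned share.** From Sample size: 3 × 100 + 2 × 200 = 700, which reproduces the stated total. The HF-PEF share is 200/700 = 28.6%, or 200/800 = 25.0% if the additional controls are extra. Recruitment choices alone move it: 200/600 = 33.3% without healthy controls, and 200/400 = 50% with Groups 3 and 4 only.

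**Formulas.** With sensitivity Se, specificity Sp and prevalence p:
- PPV = Se·p / [Se·p + (1 − Sp)(1 − p)]
- NPV = Sp(1 − p) / [Sp(1 − p) + (1 − Se)p]
- Accuracy = Se·p + Sp(1 − p)

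The article gives no Se, Sp or clinic prevalence, so those used below are assumptions.

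**Step 1: prevalence alone (Se = Sp = 0.80).**

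| Prevalence | PPV | NPV |
|---|---|---|
| 10% | 30.8% | 97.3% |
| 25.0% (200/800) | 57.1% | 92.3% |
| 28.6% (200/700) | 61.5% | 90.9% |
| 50% | 80.0% | 80.0% |

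For example, at 10%: 0.08 / (0.08 + 0.18) = 30.8%. The planned share overstates PPV for a 10% setting and understates it for a 50% setting. NPV errs the other way.

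Accuracy stays at 80% in every row because Se = Sp. When they differ it moves: with Se 0.90 and Sp 0.70 it is 72.0% at 10%, 75.7% at 28.6% and 80.0% at 50%.

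**Step 2: case mix, prevalence held at 28.6%.** All three definitions in Table 1 need HF symptoms and signs and an LVEF of about 50% or more. Group 1 is described as generally asymptomatic, Group 4 has an LVEF below 45% and Group 5 is healthy. These groups, 400 of the 500 planned non-HF-PEF participants, should largely fail the definitions by construction. Assume Se 0.80, Sp 0.60 in Group 2 and Sp 1.00 in Groups 1, 4 and 5:
- True positives 0.80 × 200 = 160; false negatives 40.
- False positives 0.40 × 100 = 40; true negatives 60 + 400 = 460.
- Pooled specificity 460/500 = 92%.
- Cohort PPV 160/200 = 80%, NPV 460/500 = 92%, accuracy 620/700 = 88.6%.

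Using the Group 2 specificity alone at the same share, PPV = (0.80 × 2/7) / (0.80 × 2/7 + 0.40 × 5/7) = 1.6/3.6 = 44%. That fall of about 36 points involves no change in prevalence.

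**Step 3: both together.** At 20% prevalence with Sp 0.60, PPV = 0.16 / (0.16 + 0.32) = 33%. Of the 47 points between 80% and 33%, about 36 are case mix and 11 prevalence. Changing prevalence first (Sp 0.92 at 20%: 0.16/0.224 = 71%) attributes 9 points to prevalence and 38 to case mix.

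**The case against.** The strongest reply is that the three definitions are compared in one cohort, at one prevalence, to inform new criteria. Nothing in the article offers their PPVs as clinic probabilities. Sensitivity and specificity are also planned, so a reader can convert them. This limits the harm and lowers the severity, but raw PPV and NPV still describe no clinical population, and conversion from a pooled specificity would carry the case mix along.

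Two possible remedies in the article do not reach the point. Clinical outcomes admits selection and referral biases, but its administrative data address health service use and outcomes. External validation is placed under the Phase 4 score, not the three existing definitions.

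Some stronger readings are tempting but unsupported:
- *Prevalence is fixed at 28.6%.* Three targets are upper limits, the sample may be increased, 649 were enrolled at the last count, and a blinded panel may reclassify. The share is driven by recruitment, not fixed by it.
- *PPV is always flattered.* Step 1 shows that the direction depends on the target setting.
- *A contrast such as 80% against 33% measures the prevalence problem.* Step 3 shows that it is mostly case mix, and it rests on assumed perfect specificity in three groups.
- *Systolic HF patients are not candidates for the test.* Ejection fraction is part of every definition, so a patient with HF symptoms is a candidate until it is known. Group 4 is also the declared comparator for Group 3.
- *Only Group 2 specificity counts.* The article does not say that Group 2 is symptomatic, and it names hypertension, diabetes and obesity, which are Group 1 entry conditions, among the mimics.
- *The score's certainty bands need recalibrating.* They are to be set by a panel-based method, with no stated probability model tied to the planned share.

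**Conclusion.** The point holds as a moderate correction to analysis and reporting. Applied as written, PPV and NPV, and accuracy whenever sensitivity and specificity differ, would be properties of the recruitment scheme. Under an assumed 80% sensitivity and specificity, PPV runs from 30.8% to 80% over prevalences of 10% to 50%, with 61.5% at the planned share. Under the separate case-mix assumptions, PPV is 80% pooled and 44% with the Group 2 specificity. These sizes are illustrations, since the article supplies no performance or prevalence figures. The dependence itself needs no assumption for PPV and NPV beyond an imperfect definition.

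A reader might infer that the diagnostic comparison is invalid or that the design must change. The documents do not support that: the cohort, the blinded panel and the comparison of the three definitions all stand.

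**What to change.** In the Adjudication section, make three changes:

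1. Name as main results sensitivity, specificity in each adjudicated non-HF-PEF group, and likelihood ratios, all with confidence intervals. State which specificity each likelihood ratio uses. In the Step 2 example the positive ratio is 0.80/0.08 = 10 with pooled specificity and 0.80/0.40 = 2 with that of Group 2.
2. Replace raw cohort PPV and NPV with values from Bayes' rule over a stated prevalence range, for example 10% to 50%, for each definition, again naming the specificity used.
3. If raw cohort PPV, NPV or accuracy are still shown, label them as specific to this sample and not transportable.

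The cost is revised wording and one extra table. No new data are needed, and recruitment is unaffected. The predictive values may look less favourable than the raw ones.

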**Figure 2 F2:**
[figure not shown]
Alberta HEART adjudication process.

#### Phase 1

In the first phase, the adjudicators will be asked to group the participants into one of the 5 groups above, using pre-enrollment (i.e. no study related variables) clinical criteria. We will then test the current definitions as to their validity.

#### Phase 2

In the second phase, information from the study echocardiogram and cardiac MRI will be used to re-adjudicate participants and explore if the clinical phenotype can be better enhanced using standardized imaging biomarker information.

#### Phase 3

In the third phase, data from the clinical phenotype, novel imaging markers, and biomarker testing to see if it can identify distinct patient cohorts. This will also incorporate novel imaging or biomarkers that are emerging or have not been previously validated.

#### Phase 4

In the final phase, all of the above will be integrated to develop a *de novo* diagnostic system via a panel-based method. Potential criteria will be viewed singly and together in order to develop a novel diagnostic scoring system with the following principles: (1) clinical symptoms and signs must be included as a basis for the diagnosis of HF-PEF; (2) diagnostic certainty should be categorized into definite, probable, possible, and not present; (3) time of evaluation must be included with respect to acute events; (4) no binary LVEF cutoff exists therefore a spectrum of LVEF will be used; (5) areas to be considered as candidate variables for evaluation should include mechanical, electrical, biomarker, and imaging modalities and should be done at rest and with provocation of exercise; (6) subtypes of HF-PEF likely exist based on etiology or mechanism of dysfunction and these subtypes likely include, but are not limited to, ventricular-vascular decoupling, myocyte dysfunction, infiltration, valve-related, extracellular matrix hypertrophy**,** post-operative and arrhythmia-related, especially atrial fibrillation; and (7) a simple clinical tool will be adopted if valid and clinically relevant, so attention to the end-user will be incorporated at an early stage through interaction with end-users (see http://www.albertaheartresearch.ca). External validation will be sought in existing datasets including MAGGIC, CHARM and the Olmsted County database.

### Imaging– MRI and echocardiography

Most diagnostic constructs for the identification of HF-PEF, such as those from the European Society of Cardiology (Table 
1)
[14], employ imaging-measures of diastolic function in a diagnostic algorithm. However, these are used as binary variables and cut-points considered important for the diagnosis of HF-PEF. Several new quantitative imaging tests are available that more directly measure the physical mechanisms during ventricular relaxation that are associated with diastolic function, such as ventricular untwisting and global tissue strain rates, or that reflect tissue characteristics including diffuse and focal fibrosis and edema.

Thus, our goal is to evaluate a wider array of imaging tests for the purpose of defining a new set of practical criteria for the characterization of diastolic dysfunction that would be widely available. In addition to standard measures, main features will be evaluated using one or both of echocardiographic and CMR imaging: (1) ventricular stiffness
[24,25]; (2) ventricular relaxation
[24,26]; and (3) ventricular-vascular coupling
[27,28]. This new approach will address the significant variability (often due to load dependence) and low specificity of the conventional imaging parameters of diastolic function and develop load-independent measures.

In brief, the CMR scans will be performed on a 1.5 T magnet (Sonata, Siemens and Avanto, Siemens) and will include an assessment of: (1) atrial and ventricular volumes and function using steady state free precession (SSFP), (2) myocardial tissue characterization using late gadolinium enhancement (LGE) as well as quantitative T1 and T2 imaging, (3) estimation of ventricular and vascular stiffness using SSFP, phase contrast and tagging techniques and (4) pulmonary water content. For LGE and T1 imaging, 0.15 mmol/kg of gadolinium contrast (Gadovist, Bayer) will be given intravenously. Cardiac volumes and function and myocardial scar will be analyzed using commercially available software (Syngo, Siemens and CMR42, Circle) by experienced interpreters blinded to the study group assignment. Other measures of cardiac function and myocardial tissue characterization as well as vascular function and pulmonary water content will be performed using custom built software (MATLAB).

2D and 3D echocardiography will be performed on IE 33 (Philips) scanners with and without intravenous injection of the ultrasound contrast agent Definity. In addition, recordings using color, spectral, tissue Doppler and speckle tracking imaging will be obtained according to the American Society of Echocardiography (ASE). The following measurements will be performed by two experienced observers according ASE standards: LV volumes, ejection fraction, LA volumes, RV size and function, quantification of valvular lesions, systolic pulmonary artery pressure, mitral/tricuspid inflow velocities, mitral/tricuspid annular velocities, global longitudinal strain and strain rate. The recordings will also be processed using custom built software for fusion of 3D datasets and new tools to assess myocardial deformation which promise a more reliable assessment of volume changes as well as systolic and diastolic LV/RV function.

